### Data management and analysis

Data management will follow procedures established by the AASH (see Jobarteh ML *et al.* Developing a ‘Whole Child Approach’ to understanding and preventing child stunting: the UKRI GCRF Action Against Stunting Hub. *BMJ Paed. Open* 2023). This includes a data sharing strategy that will build on the guiding principles for scientific management and stewardship and Concordat on Open Research Data to ensure equitable access to data.

For microbiota analysis, FASTQ files containing 16S rRNA gene amplicon sequences will be processed using well-validated software pipelines such as mothur^30^ or DADA2.^31^ These pipelines include various quality control steps and will produce final output tables containing the proportional abundances of various microbiota taxa in each sample. They can also generate various metrics of bacterial diversity within and between samples. These data will be visualised in the form of dendrograms, ordination plots, heatmaps and box plots. Microbiota 16S rRNA gene sequence data will be released publicly via the European Nucleotide Archive at the end of the study.

Multilevel models taking into consideration aggregate units such as geographical setting will be used to investigate associations between enteropathogens/gut parasites, biomarker concentrations and LAZ, to assess longitudinal associations between biomarker concentrations and growth rates, and to determine which biomarkers, enteropathogens and/or characteristics of the gut microbiota are associated with stunted growth at specific time points. In addition, Bayesian methods, using directed acyclic graphs, will be used to investigate a variety of possible interactions between gut health indices and linear growth (stunting) and to assess combinatorial effects of the diverse elements of gut health (expressed as categorical or continuous variables, as appropriate) on stunting. When the data being analysed include repeated measurements from the same individual, random intercept models will be employed. The number of missing data points for each variable of interest will be reported and the distributions of key variables will be tabulated to compare individuals with and without complete data. Analyses will be carried out both on datasets where multiple imputation will be implemented, and on datasets that will be restricted to complete cases.

To allow for interdisciplinary analyses and the development of the typology of stunting, multilevel modelling and Bayesian methods will be extended to integrate cohort data collected in other workstreams. Stata V.17 and other appropriate software will be used for the analysis.

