### Sample size determination

Sample size calculations were performed in R with the package ‘pwr’ and were based on a multiple linear regression analysis with 10 predictors, an effect size of 0.035, power of 80%, significance level of 0.05 and drop-out rate of 20%. These calculations resulted in a total of 592 participants per site.

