### Study procedures

#### Sample collection

Stool samples will be collected from pregnant women in the third trimester. In infants/children, stool samples will be collected either at a health facility or in the participants’ homes at ages 1 month, 6 months and 24 months. For stool samples collected at home, study staff will visit either on the day before or on the morning of sample collection to provide the mother/carer with a disposable nappy or plastic sheet, sample collection containers with spatula, plastic specimen bag, small cold box with ice pack and a bar of soap. The staff will explain the sample collection procedure to the mother/carer through verbal and pictorial information, and the staff will check the procedure is understood. Mothers/carers will be asked to snugly fit a nappy or plastic sheet to the infant last thing at night and collect the next stool produced by the infant, either by pouring it from the nappy/sheet if the sample is loose, or using the spatula if it is formed, and fill the sample containers. They will place the filled container in the specimen bag and then in the cold box and wash their hands with soap. Field staff will return later the same day or the following day to label the sample and transfer it to the laboratory. Subject to agreement with the mother/carer, this process will be repeated over the following 14 days until an adequate stool sample is obtained (at least 5 mL of liquid stool or 5 g of formed stool). To avoid dilution of biomarkers in children suffering from acute diarrhoea, stool collection will be delayed until the stools have returned to their usual consistency. Based on the WHO definition,^21^ acute diarrhoea will be considered as significantly more frequent or loose/watery stools in the mother’s/carer’s opinion in exclusively breastfed babies and three or more liquid stools in the last 24 hours in children receiving other feeds. Mothers/carers will be fully briefed on recognising acute diarrhoea as distinct from loose stools within exclusively breastfed babies. During the visits to collect samples at age 6 and 24 months, trained research staff will collect 2.5 mL venous blood. Subject to the agreement of the mother/carer, efforts will be made to limit attempts to collect the required blood volume to three. Finally, early morning urine samples will be collected from pregnant mothers and infants at 6 and 24 months in Senegal to identify the presence and intensity of *Schistosoma haematobium* and hybrids therein. All samples will be transported to laboratories in a cold box. The time between sample collection and receipt in the laboratory will be recorded. Pilot testing of sample collection processes was conducted in each country.

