
Anthropometric measurements (including length and weight) will be taken in duplicate from infants at birth, 3, 6, 9, 12 18 and 24 months of age as described in detail in another protocol in this UKRI GCRF Action Against Stunting Hub supplement (Davies-Kershaw H *et al.* Anthropometric, biochemical, dietary, morbidity and well-being assessment in women and children in Indonesia, India and Senegal: a UKRI GCRF Action Against Stunting Hub protocol. *BMJ Paed. Open* 2023). Z-scores for length-for-age (LAZ) will be calculated using the 2006 WHO Growth Standards and stunted growth will be defined as an LAZ <-2 SD.^2^

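### Random intercepts are the only within-child structure named for repeated measurements, which can understate standard errors if growth rate is tested as a biomarker-by-age effect over three or more visits

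*Protocol article*

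**What the plan says.** Under Data management and analysis the model family is described as follows: "Multilevel models taking into consideration aggregate units such as geographical setting will be used". Three uses are listed: associations with LAZ, associations with stunting at given time points, and, between them, "to assess longitudinal associations between biomarker concentrations and growth rates". For within-child dependence the paragraph gives one rule: "When the data being analysed include repeated measurements from the same individual, random intercept models will be employed". It mentions no random slope, residual correlation structure or robust standard error. It does not say whether growth rate enters as an age interaction in a model for LAZ or as a derived velocity.

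The schedule is under Sample collection. Length and weight "will be taken in duplicate from infants at birth, 3, 6, 9, 12 18 and 24 months of age", which is seven occasions. Infant stool is collected "at ages 1 month, 6 months and 24 months". For blood: "During the visits to collect samples at age 6 and 24 months, trained research staff will collect 2.5 mL venous blood". Infant biomarkers are therefore measured two or three times, and maternal stool in the third trimester.

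**The concern.** A random-intercept model lets children differ in level but not in rate of growth. It also treats any two LAZ values from one child as equally correlated, whether three months or two years apart. The growth-rate aim presupposes that children do differ in slope, and a biomarker is unlikely to explain all of that difference. The unexplained slope variation falls into the residual. There it is averaged over all within-child degrees of freedom, although each child supplies only one slope. For a child-level biomarker, the biomarker-by-age coefficient is then judged against a standard error that is too small.

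An added level for geographical setting does not help, because the missing variation is between children within a setting. Reporting both multiply imputed and complete-case results does not help either, because both would use the same covariance structure. The Conclusions section says the study should identify biomarkers to serve as outcome measures in later trials, so a spurious association with growth rate could be carried forward.

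**Working it through.** **The plan's own figure.** The protocol states no standard error or error rate for the repeated-measures models. Its one computed figure, 592 per site, is "based on a multiple linear regression analysis with 10 predictors". With f² = 0.035, 80% power and alpha 0.05, the noncentral F calculation gives v = 462.3 and N = 462.3 + 10 + 1 = 473.3. Then 473.3/0.8 = 591.6, rounded up to 592. The figure reproduces but does not bear on this point.

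**Inputs.** From the protocol: ages 0, 0.25, 0.5, 0.75, 1, 1.5 and 2 years, so n = 7. Assumed, because the documents give no values: SD of true LAZ slopes τ = 0.1 to 0.5 per year, and residual SD s = 0.3 to 0.6. Also assumed: linear trajectories, independent residuals, complete visits, and a biomarker constant within child (for example a maternal value or one taken at a single age).

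**Spread of ages.** The ages sum to 6 and their squares to 8.125, so Sxx = 8.125 − 36/7 = 2.98.

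**Variances of the biomarker-by-age coefficient**, up to a common factor:
- true: τ² + s²/Sxx
- reported by the random-intercept model: s²/Sxx + τ²/(n − 1)
- ratio: R = (τ²Sxx + s²) / (s² + τ²Sxx/(n − 1))

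The standard error is too small by a factor √R. The actual error of a nominal 5% test is 2[1 − Φ(1.96/√R)]. The number of children cancels.

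**Worked case, τ = 0.4 and s = 0.4.** τ²Sxx = 0.16 × 2.98 = 0.477. R = (0.477 + 0.16)/(0.16 + 0.477/6) = 0.637/0.240 = 2.66, √R = 1.63, and the type I error is about 23%.

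**Type I error, seven visits:**

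| Residual SD | τ = 0.1 | 0.2 | 0.3 | 0.4 | 0.5 |
|---|---|---|---|---|---|
| 0.3 | 8.1% | 15.6% | 22.9% | 28.4% | 32.1% |
| 0.4 | 6.8% | 11.6% | 17.5% | 22.9% | 27.2% |
| 0.5 | 6.1% | 9.4% | 13.9% | 18.7% | 22.9% |
| 0.6 | 5.8% | 8.1% | 11.6% | 15.6% | 19.5% |

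**Simulation** (480 children, 4,000 runs per setting, s = 0.4). At τ = 0, 0.1, 0.2, 0.3, 0.4 and 0.5 the random-intercept test rejected in 5.4%, 7.1%, 12.9%, 17.4%, 22.0% and 27.5% of runs. Regressing each child's own slope on the biomarker, which in this balanced setting is equivalent to a random-slope model, rejected in 5.0% to 5.4%.

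**Other visit sets:**
- Five LAZ visits from 6 to 24 months (6, 9, 12, 18, 24): Sxx = 8.0625 − 5.75²/5 = 1.45. At τ = 0.3, R is 1.80 with s = 0.3 and 1.25 with s = 0.6, giving about 14% and 8%.
- Three LAZ visits (birth, 6, 24 months): Sxx = 2.17. At τ = s = 0.4, R = 0.507/0.333 = 1.52, giving about 11%.
- Two visits (6 and 24 months): n − 1 = 1, so R = 1 and the error is 5.0% at any τ. Simulation gave 4.9% to 5.3%.

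Biomarkers that change with age within a child are not covered by this formula and are not sized here.

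**The case against.** A reader might infer that the protocol commits itself to random-intercept-only models, so that growth-rate standard errors will be far too small and false positives are assured. The documents do not support that reading.

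- The sentence names random intercepts but does not rule out random slopes or robust errors. This is a condensed article, and an unseen analysis plan may add them.
- A biomarker-by-age term is an inference. A growth rate derived per child and used as the outcome does not have this error. In a model of repeated interval velocities, a random intercept is itself a child-specific growth rate.
- Plasma markers exist only at 6 and 24 months, and pairing them with LAZ at those two ages gives no inflation.
- The size depends on two SDs that the documents do not give. At the mild end (slope SD 0.1, residual SD 0.6) the error is 5.8%, which is hardly a defect.
- Growth rate is one of several aims. No primary analysis is designated, and 0.05 appears only in the sample-size paragraph, so talk of biomarkers being declared positive goes beyond the text.

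All of this stands and limits the claim. It does not remove it. The rule is stated without condition for any repeated measurements, in the paragraph that sets the growth-rate aim under multilevel models. An analysis plan that followed it literally for LAZ trajectories would carry the problem forward.

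**Conclusion.** The point holds conditionally. The one within-child structure the protocol names is not adequate for a biomarker-by-age analysis of LAZ over three or more visits when children differ in true slope. Across the assumed grid at seven visits, the standard error is too small by a factor between about 1.03 (slope SD 0.1, residual SD 0.6) and 1.97 (0.5 and 0.3). The corresponding type I error is about 6% to about 32%. These sizes rest on the assumed SDs, a biomarker constant within child and complete data. Two-occasion analyses and analyses of a per-child growth rate are unaffected. The remedy is to clarify and amend the sentence. The documents do not show that any result will be wrong.

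**What to change.** Amend the random-intercept sentence in Data management and analysis along these lines: for analyses of LAZ trajectories or growth rates that use three or more visits per child, models will include a random intercept and a child-level random slope for age, with their covariance estimated (or an unstructured within-child covariance over visits, or robust standard errors clustered by child); the growth-rate association is the biomarker-by-age term; models with a random intercept only are kept for analyses of two occasions. The threshold should be three visits, because at birth, 6 and 24 months the error is already about 11% at the 0.4 and 0.4 assumption. If a derived per-child velocity is intended instead, saying so would also settle the matter.

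The cost is one sentence, wider intervals for growth-rate effects, somewhat heavier computation and occasional convergence checks. Data collection and the sample-size calculation as stated do not change.

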### Patient and public involvement

There was no involvement of patients or the public in the design of this study.

## Discussion

The limited impact of interventions to prevent or ameliorate stunting in young children in low-resource settings has resulted in a renewed interest in the role of gut health. The AASH cohorts will be among the largest investigating the inter-relationships between gut colonisation with bacterial, protozoal and helminth pathogens, the gut microbiota and biomarkers of EED, and their impact on linear growth in populations with different prevalence rates of stunting (moderate to high) and environmental conditions.

The AASH offers the opportunity to compare gut health characteristics and their association with stunting across three distinct geographical settings. This is particularly important as there is limited evidence to date regarding the role of gut health in children in West Africa and Southeast Asia. In addition, our findings will be integrated with data collected in other AASH workstreams to advance scientific understanding of how gut health interacts with other host and environmental factors that underlie common typologies of stunting and increase the evidence base for future intervention studies. This evidence base will be further strengthened by the investigation of elements of maternal gut health as novel drivers of poor gut health and stunted growth in infants. Harmonised procedures to collect, manage and analyse data and samples across the countries will greatly enhance the validity of our findings.

In low-income settings, there is a need to further investigate biomarkers of intestinal structure and function to identify acceptable and affordable tools that can be scaled up at the population level to diagnose and monitor EED. Further, it is of interest to identify possible geographic-specific and seasonal variations in the association between these biomarkers and stunting. The selection of biomarkers for this study was informed by previous reports of their utility in reflecting the aetiopathogenesis of EED and association with linear growth faltering.^10 12 13 15 16^

This study will have some limitations. Although our study design allows us to explore similarities and differences across cohorts from three countries, our findings may not be generalisable to gut health and growth in other low-resource settings where the intensity of infection, characteristics of the gut microbiota and pathology of EED may differ. In general, it is a challenge to move from associations to an understanding of causality in an observational study. However, the SENeGal SYNbiotic (SENGSYN) study, a clinical trial nested within the AASH investigating the effect of supplementation with synbiotics on growth and biomarkers of gut health (seeMomo Kadia B *et al*. Improving gut health and growth in early life: a protocol for an individually randomised, two-arm open-label, controlled trial of a synbiotic in infants in Kaffrine District, Senegal. *BMJ Paed Open* 2023), may build on associations between gut health and growth determined in the observational cohorts to provide evidence of causality. From a technical perspective, our method of stool collection using cold boxes and minimising time between sample provision and processing in the laboratories is pragmatic. However, we cannot exclude the possibility that changes in stool biomarkers, pathogens and the microbiota may occur during transfer. We will, however, assess whether time between collection and receipt in the laboratory is associated with the results of the various analyses. We also acknowledge that providing a picture-based reference chart for mothers/carers to assess stool consistency would be an even more robust approach to assess stool consistency for the exclusion of diarrhoeal samples. Nonetheless, as part of quality control, trained laboratory technicians will cross-reference all collected samples to ensure they are of appropriate consistency before being further processed. Furthermore, we acknowledge that the WHO Child Growth Standards do not necessarily provide a good statistical fit to each country, but these internationally approved standards are widely accepted and facilitate cross-country comparisons, which is considered particularly important when including the three countries in this study. Previous multicountry studies, notably the Malnutrition and Enteric Disease study study,^2^ have used the same growth standards.

## Conclusions

The findings of this study will improve scientific understanding of how gut health contributes to stunting, either directly, or through interlinks with the wide range of host- and environmental factors (including maternal gut health characteristics) monitored in the AASH project, and how these may vary between different geographical locations. Our findings will inform the development of diagnostic- and management options for EED and identify biomarkers of gut health that may serve as outcome measures in future intervention trials in resource-constrained settings.

10.1136/bmjpo-2022-001637.supp1Supplementary data

## Data Availability

No data are available. Data sharing is not applicable to this manuscript as it describes a protocol.
